### 5.3 Selection procedures (entry procedures)

Written informed consent for the study must be obtained prior to randomization. Key baseline patient characteristics will be recorded on the Case Report Forms (CRFs). Results of tests to confirm inclusion/exclusion criteria will be maintained in the patient files. Treatment allocation will be performed as stated above (see 3.3). Baseline CRFs should be completed soon after randomization.

### 5.4 Encouraging compliance

Noncompliance is not expected to be a major issue in this trial. The interventions are simple and the surgical intervention occurs at a single time-point and is controlled by the treating physician,

outcomes are objective, and data-forms are concise. Patient compliance to the study supplements will be monitored at follow-up visits via pill counts.

Patients are generally followed by their surgeons/cardiologists for several years after their procedure, and it is expected 99.9% follow-up at one month and over 99% follow-up at 6 months will be obtained. PHRI has substantial experience in documenting vital status in >99.5% in its clinical trials involving over 200,000 subjects recruited from over 50 countries and followed for up to 8 years. This expectation will be met in this study, especially with a post-surgical population in whom clinical follow-up by the surgeon for a minimum of 3 months is generally routine.

The overall study has been designed such that only one SVG is required to facilitate recruitment. We did consider restricting the study to patients who required at least 2 SVGs, as the event rates would presumably be greater. The chosen protocol does allow patients who are having only 2 grafts constructed (ITA and 1 SVG) and is compatible with patients undergoing more extensive arterial revascularization. We anticipate that the average number of vein grafts/patient will be 1.5 (as in GRIIP) (6). We considered restricting the control group to open harvesting rather than allow for endoscopic harvesting to be performed as well. We thought it important to include endoscopic harvesting as it is a commonly used technique, and there is recent evidence that endoscopic vein harvesting purports worse patency and clinical outcomes than conventional SVG harvesting (50). Although endoscopic patients will usually be unblinded, endpoint adjudication is blinded. Our post-hoc analysis will also aim to elucidate any difference in graft patency in the control SVGs harvested in the conventional open versus endoscopic techniques. We expect that the RRR will be similar or greater comparing endoscopic and no-touch versus open control and no-touch.

The operator dependence of the “no touch” technique, along with endoscopic vein harvesting at particular institutions, may impact on the outcomes determined. A multi-centre approach should allow for this to become evident and allow for the valid conclusion about the ability to generalize the intervention, irrespective of its benefits.

## **5.5 Study measurements**

### **Study Outcomes**

#### **Primary Outcome**

***Surgical Intervention:*** The ***proportion of study SVGs*** (“no touch” versus conventionally harvested) which are totally (100%) occluded on 64-slice cardiac CT angiography at 1-year post-CABG and death due to cardiovascular or unknown causes.

***Pharmacological Intervention:*** The ***proportion of patients*** with  $\geq 1$  graft totally (100%) occluded on 64-slice cardiac CT angiography at 1-year post-CABG and death due to cardiovascular or unknown causes, comparing the fish-oil to placebo groups. Fish oils can theoretically affect patency of any of the bypass grafts (study or non-study, saphenous veins or arterial), although the effect would presumably be greatest in saphenous veins. We have therefore defined the primary outcome

for the pharmacologic intervention as the proportion of patients with at least 1 graft occluded (saphenous or arterial).

Any clinically directed angiogram (CTA or conventional) occurring up to 15 months postoperatively will contribute to the primary endpoint. Patients with poorly controlled atrial fibrillation or claustrophobia will be approached for conventional angiography. We anticipate from past experience that this will apply to <2% of patients.

## **Secondary Outcomes**

***Surgical Intervention:*** The two groups will be compared with respect to:

- i. The number of study SVGs with a significant (50-99%) stenosis on 1-year CTA.
- ii. The number of study SVGs with a significant stenosis or total occlusion at 1-year CTA.
- iii. The incidence of and severity of adverse SV harvesting events by 1-year (infection, haematoma, swelling, neuropathy).
- iv. The incidence of the composite endpoint of perioperative and 1-year non-fatal MI (using new definition, see “Early perioperative myocardial infarction (within 72 hours of surgery)” below), all-cause mortality, repeat revascularization (redo CABG or PCI) (major adverse cardiac events, MACE) and stroke.

***Pharmacological Intervention:*** The two groups will be compared with respect to:

- i. The proportion of patients with  $\geq 1$  graft with a significant (50-99%) stenosis on 1-year CTA.
- ii. The proportion of patients with  $\geq 1$  graft with a significant stenosis or total occlusion at 1-year CTA.
- iii. The proportion of venous and arterial grafts considered separately with total occlusion and/or stenosis, defined above.
- iv. The incidence of the composite endpoint of perioperative and 1-year non-fatal MI (using new definition (see “Early perioperative myocardial infarction (within 72 hours of surgery)” below), death, repeat revascularization (redo CABG or PCI) (major adverse cardiac events, MACE) and stroke.

NB: Graft occlusion determines the primary endpoint and graft stenosis, the secondary endpoint, as graft occlusion is generally of greater clinical importance than stenosis. Graft occlusion is the primary mode of SVG failure 1 year postoperatively (7).

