## **2 STUDY OBJECTIVES**

The objective of the pilot phase of the study is to determine the number of eligible patients of the total isolated CABG patients, the consent rate, adherence to the protocol including rate of follow-up cardiac CT angiography, medication discontinuation and the overall incidence of the primary outcome. Achieving a recruitment rate of 1-2 patients/centre/month will determine if the study will proceed to the full phase III trial.

The primary objective of this study for the **Surgical Arm** is to determine whether a novel atraumatic (“no touch”) technique of pedicled saphenous vein graft (SVG) harvesting results in a lower **proportion of study SVGs** that are totally (100%) occluded on 1-year post-CABG angiography and death due to cardiovascular or unknown causes, compared to conventional SVG harvesting techniques, in patients undergoing CABG.

The primary objective of this study for the **Pharmacological Arm** is to determine whether N-3 polyunsaturated fatty acid (fish oil) oral supplementation results in a lower **proportion of patients** with  $\geq 1$  graft (study SVG, non-study SVG or arterial graft) totally (100%) occluded at 1-year post-CABG angiography and death due to cardiovascular or unknown causes, compared to those who received placebo.

The secondary objectives for the **Surgical Arm** are to determine whether:

- i. The “no touch” technique of SVG harvesting results in a lower ***proportion of study SVGs*** that have a significant stenosis (50-99%) on 1-year post-CABG angiography compared to conventional SVG harvesting techniques.
- ii. The incidence and severity of adverse SVG harvesting events at 1-year post-CABG (infection, haematoma, swelling, neuropathy, quality of life measures) are similar between the “no touch” and conventional groups of patients.
- iii. The incidence of the composite of non-fatal myocardial infarction (MI) (using new definition, see Section 5.5), all-cause mortality, and repeat revascularization (redo CABG or percutaneous coronary intervention [PCI]) perioperatively and at 1 year is lower in the “no touch” versus conventional group of patients.

The secondary objectives for the **Pharmacological Arm** are to determine whether:

- iii. Fish oil supplementation results in a lower ***proportion of patients*** with  $\geq 1$  graft with a significant (50-99%) stenosis at 1-year post-CABG angiography, compared to those who received placebo.

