### **8.3 Statistical Methods**

The primary comparison for the 2 main study questions (“no touch” vs. conventional SVG harvesting [primary endpoint: study SVG occlusion]; fish oil supplementation vs. placebo [primary endpoint: proportion of patients with >1 graft occluded]) will be performed using a Chi-square test according to the intention-to-treat principle. A test for interaction will be tested similarly and with logistic regression. Statistical significance is assumed for  $p < 0.05$ . The secondary graft occlusion endpoints, graft stenosis, or graft occlusion or significant stenosis, will also be tested with Chi-square or Fisher’s tests where appropriate, considering graft stenosis as a dichotomous variable, as well as logistic regression treating graft stenosis as an ordinal variable. Additional modeling will be performed post hoc with logistic regression, generalized estimating equation and bootstrapping techniques, to evaluate covariates of graft occlusion (7,18,71). Variables of interest in addition to the usual demographic factors include: open vs. endoscopic vein harvesting, serum lipid values; study centre; surgeon; time period of patient entry (to address a possible learning effect); timing of postoperative angiography; parameters related to the distal coronary artery target such as, size, quality, and factors related to the specific coronary artery grafted including the severity of the proximal stenosis. Other categorical outcomes (major cardiac events and vein harvest site complications) will also be compared with either Chi-square or Fisher’s Exact test where appropriate. The harvest site infection scores will be tested using t tests.

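### Fish-oil secondary outcome iii is counted per graft but falls under tests that treat grafts in one patient as independent; as a minor point, the stenosis objectives name only the 50-99% band, in which an occluded graft is a non-event.

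*Protocol*

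**What the plan says.** **Graft-level outcome.** The third fish-oil secondary outcome in Section 5.5 is "The proportion of venous and arterial grafts considered separately with total occlusion and/or stenosis, defined above". Its unit is the graft. Section 3.3 randomises patients, and Section 5.4 expects 1.5 vein grafts per patient on average. Arterial grafts come on top: Section 5.1 requires an internal thoracic artery graft in every patient and allows more.

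**Planned test.** Section 8.3 states: "The secondary graft occlusion endpoints, graft stenosis, or graft occlusion or significant stenosis, will also be tested with Chi-square" or Fisher's tests, "considering graft stenosis as a dichotomous variable, as well as logistic regression treating graft stenosis as an ordinal variable". GEE appears once, in the next sentence: "Additional modeling will be performed post hoc with logistic regression, generalized estimating equation and bootstrapping techniques, to evaluate covariates of graft occlusion". No clustered method is assigned to a treatment comparison.

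**Stenosis endpoints.** Surgical secondary outcome i in Section 5.5 is "The number of study SVGs with a significant (50-99%) stenosis on 1-year CTA". Outcome ii follows directly: "The number of study SVGs with a significant stenosis or total occlusion at 1-year CTA". The fish-oil arm has the same pair at patient level. The Section 2 objectives carry only the first of each pair; for the surgical arm, the proportion of study SVGs "that have a significant stenosis (50-99%) on 1-year post-CABG angiography compared to conventional SVG harvesting techniques". The combined measure does not appear in the objectives. The protocol does not say whether occluded grafts stay in the denominator of the 50-99% measure.

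**The concern.** **Clustering.** Fish oil is a systemic treatment given to a patient, and Section 5.5 itself notes that it could affect any of that patient's grafts. Grafts in one patient share the patient, the surgeon, the medication and the adherence. A chi-square test on pooled grafts uses the variance of independent observations. With positive within-patient correlation that variance is too small, and so is the p-value.

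**Stenosis only.** A 100% occluded graft lies outside 50-99%. Treated as a dichotomy over all study SVGs, the worst result is counted with the grafts free of significant stenosis. An arm with fewer occlusions has more open grafts in which a stenosis can be found. Success on the primary endpoint therefore pushes this secondary objective the wrong way.

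**Working it through.** **The plan's own figure.** For 20% versus 14% occlusion, two-sided alpha 0.05 and 80% power, the usual two-proportion formula (pooled variance, no continuity correction) gives 615 per group, as Section 8.5 states. The sample size is not in dispute.

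**Clustering**

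Inputs: a mean of 1.5 vein grafts per patient (Section 5.4). Assumptions, not in the protocol: half the patients have one vein graft and half two; intraclass correlation (ICC) 0.05 to 0.5.

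- Mean graft number: E[m] = 0.5×1 + 0.5×2 = 1.5. Mean square: E[m²] = 0.5×1 + 0.5×4 = 2.5.
- Weighted cluster size: 2.5/1.5 = 1.667.
- Design effect: DE = 1 + (1.667 − 1)×ICC.
- True two-sided level of a nominal 5% test: 2×(1 − Φ(1.96/√DE)).

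| ICC (assumed) | DE | True level |
|---|---|---|
| 0.05 | 1.03 | 5.4% |
| 0.1 | 1.07 | 5.8% |
| 0.3 | 1.20 | 7.4% |
| 0.5 | 1.33 | 9.0% |

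A beta-binomial simulation over the same ICC range, with 615 patients per group and 20% occlusion, gave 5.1% to 9.1%. A mix of 60% with one, 30% with two and 10% with three vein grafts (also mean 1.5) gives 5.5% to 9.8%.

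The protocol's planning rates do not establish a positive ICC. With 20% of vein grafts occluded, independence and the half-and-half mix, the share of patients with at least one occluded vein graft is 0.5×0.20 + 0.5×(1 − 0.80²) = 0.10 + 0.18 = 28%. The planned 30% covers any graft, arterial included.

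**Stenosis only**

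Inputs: occlusion of 20% versus 14% and 615 per group (Section 8.5). Assumption, not in the protocol: a stenosis rate c among patent grafts, equal in both groups.

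- Observed 50-99% proportion over all study SVGs: (1 − occlusion rate)×c.
- Ratio of no-touch to conventional: 0.86c/0.80c = 1.075 for any c.
- At c = 10%: 8.0% versus 8.6%, a difference of 0.6 percentage points.
- Chance of a significant result against no-touch at 615 per group: 4.5% at c = 5%, 5.7% at c = 10% and 8.2% at c = 20%. Without the artefact it would be 2.5% on that side.
- If no-touch truly cuts stenosis among patent grafts by 30%, the ratio is 0.86×0.7/0.80 = 0.7525. The endpoint still points the right way, with a 24.75% reduction. Power is 15% to 52% for c = 5% to 20%, against 86% to 97% for stenosis or occlusion.

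**The case against.** **On clustering.** Section 8.3 does not name outcome iii, so the chi-square assignment rests on its general sentence about secondary graft endpoints. GEE is already mentioned, and an analysis plan could supply the detail. Part of this stands: the point is narrow. But the protocol does state a test for this class of endpoint and places the clustered method elsewhere, so the sentence needs correcting rather than only filling out. A reader might infer that the graft-level p-values are certainly too small. The documents do not support that: it requires a positive ICC, which the protocol neither gives nor implies. A reader might also extend the problem to the other endpoints. It does not reach them: the surgical graft endpoints use one study SVG per patient, and the fish-oil primary and secondary outcomes i and ii are counted per patient.

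**On stenosis.** The remedy largely exists. Stenosis or occlusion is outcome ii in both arms, Section 8.3 adds an ordinal regression, and occlusion is the primary endpoint, so a technique that turned stenoses into occlusions would show its harm there. For fish oil the unit is the patient, so someone with one occluded and one stenosed graft still counts as an event. All of this stands and makes the point minor. What it leaves is that the objectives name only the 50-99% version, the denominator is open, and the ordinal levels are not defined. Restricting the denominator to patent grafts would give 10% versus 10% in the example, but it conditions on an outcome that the technique is meant to change.

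A stronger reading is tempting: that this objective is likely to show significant harm when the primary succeeds. If half of the prevented occlusions persisted as stenoses, the comparison would be 8% versus 11%, with 43% power; if all did, 8% versus 14%, with 92%. Nothing in the protocol supports either scenario, and in both of them stenoses really would be more frequent. These figures should not be used as the size of the problem.

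**Conclusion.** The point holds in a limited form. Under the test stated in Section 8.3, fish-oil outcome iii has the wrong variance whenever grafts within a patient are correlated. With positive correlation the true level is about 5.4% to 9.0% at a nominal 5%, given the assumed graft mix and an assumed ICC of 0.05 to 0.5. The inflation is modest because there are few vein grafts per patient.

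The stenosis-only objective carries a built-in shift of 7.5% relative against no-touch at the planned occlusion rates, if stenosis among patent grafts is equal. The ratio does not depend on the assumed stenosis rate; the 8.0% versus 8.6% and the roughly 4% to 8% chance of a significant result in the wrong direction do. This is mainly a failure to align Section 2 with Section 5.5.

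Neither part touches a primary endpoint or the sample size.

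**What to change.** - **Section 8.3:** state that fish-oil outcome iii will be compared with GEE or with standard errors clustered on the patient, for venous and arterial grafts separately.
- **Section 2 and the synopsis:** name stenosis or total occlusion (already outcome ii in Section 5.5), or an ordinal scale of under 50%, 50-99% and 100%, as the secondary stenosis objective. If the ordinal scale is chosen, define these levels in Section 8.3.
- **Section 5.5:** keep 50-99% stenosis alone as a descriptive result and state its denominator.

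The cost is a wording change in these places. It needs no new data, visits or patients, and GEE is already named in the plan.

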**CONFIDENTIAL**  
SUPERIOR SVG – 2011-06-13

commenced at this visit. Study supplements will not be administered on the day of surgery. Blood will be drawn at induction for the preoperative CK-MB (5 mL draw for preoperative CK-MB). The discharge visit will consist of a patient evaluation and blood work (5 mL draw for 24 hour post-operative CK-MB). At this time, a 3-month supply of the fish oil supplement or placebo will be given (by the Site Study Nurse). The 30-day visit will consist of a patient evaluation, assessment of leg wound, and a drug compliance check. The 3-month visit will consist of a patient evaluation, assessment of leg wound, and drug compliance check. The 6-month and 9-month visits will consist of a patient evaluation and drug compliance check. At the 3-month, 6-month and 9-months visits, a 3-month supply of the fish oil supplement or placebo will be given. The 1-year visit will consist of a patient evaluation, blood work (5 mL draw for serum creatinine), assessment of leg wound, drug compliance check, and cardiac CT angiography (acceptable window for angiography is 9-15 months postoperatively). ECG and blood work (creatinine) information will also be collected at this time as the patient will need to have these tests done prior to undergoing the CCTA. Patients with an estimated GFR < 30 mL/min will not be eligible for the study CT angiography. Patients with an estimated GFR of 30-60 mL/min may undergo the study CT angiography with renal precautions according to the institutional protocol, which may include any or all of the following: saline hydration, sodium bicarbonate loading, n-acetyl cysteine prophylaxis, and temporary stoppage of potentially nephrotoxic drugs and metformin.

**Table 1:** Schedule of follow-up

| VISIT SCHEDULE                  | Pre-op  | OR Day | Discharge | 30 Day | 3 Mth | 6 Mth | 9 Mth | 1 Year |
|----------------------------------------|----------------|---------------|------------------|---------------|--------------|--------------|--------------|---------------|
| Evaluation of Inclusion Criteria       | ✓              |               |                  |               |              |              |              |               |
| Informed Consent                       | ✓              |               |                  |               |              |              |              |               |

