**Wound complications:**

Deep mediastinal wound infection: Surgical site infection requiring surgery

Superficial wound infection: Surgical site infection not requiring surgery

Sterile wound dehiscence: Culture negative dehiscence of a wound

**Major Bleed:** Major bleeding that is defined as bleeding greater than 48 hours post-operative and associated with any of the following: death, drop in hemoglobin of at least 2 g/dL, significant hypotension with the need for inotropic agents, bleeding requiring surgical intervention [other than vascular site repair], intracranial hemorrhage, intraocular hemorrhage (excluding subconjunctival hemorrhage), or the requirement for a transfusion of at least 2 U of blood.

**Renal failure:** Requirement for renal replacement therapy (e.g., dialysis, continuous hemofiltration, renal transplant). Hemofiltration or dialysis only during cardio-pulmonary bypass does not constitute a requirement for renal replacement therapy. Patients who receive dialysis within 1 month prior to the surgery are not eligible for this endpoint.

**Repeated coronary revascularization:** New CABG procedure or PCI associated with documented ischemia by ECG *and* graft failure or new culprit lesion ( $\geq 70\%$  luminal stenosis).

**Recurrence of angina:** New onset of typical chest angina with documented ischemia by stress testing (ECG, echocardiography, or nuclear) or persistence of CCS grade  $\geq 2$  angina after the surgery.

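### Secondary graft outcomes i and ii are read on the 1-year CTA only, so they can miss grafts that failed on an earlier clinical angiogram and were reopened, including occlusions that the primary counts

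*Protocol*

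**What the plan says.** All of this is in the Protocol.

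- **Section 5.5, Primary Outcome.** After defining occlusion on the 1-year CT scan, the text widens the source: "Any clinically directed angiogram (CTA or conventional) occurring up to 15 months postoperatively will contribute to the primary endpoint". It also provides a substitute for patients who cannot have a usable scan: "Patients with poorly controlled atrial fibrillation or claustrophobia will be approached for conventional angiography".
- **Section 5.5, Secondary Outcomes, surgical.** Outcome i is "The number of study SVGs with a significant (50-99%) stenosis on 1-year CTA". Outcome ii is "The number of study SVGs with a significant stenosis or total occlusion at 1-year CTA".
- **Section 5.5, Secondary Outcomes, pharmacological.** Outcomes i and ii are the patient-level counterparts and name the same scan; ii counts patients with at least one "graft with a significant stenosis or total occlusion at 1-year CTA". Outcome iii, for venous and arterial grafts separately, refers back to these definitions.
- **Section 5.5, Secondary Outcomes, item iv in both arms.** Repeat revascularization is a component of the clinical composite.
- **Section 5.5, Definitions.** Repeat revascularization begins with "New CABG procedure or PCI associated with documented ischemia by ECG" and also requires graft failure or a new culprit lesion. Nothing is said about how the treated graft is classified afterwards.
- **Section 5.2.** For the 1-year study, the "acceptable window for angiography is 9-15 months postoperatively".
- **Section 2.** The matching surgical objective concerns study grafts "that have a significant stenosis (50-99%) on 1-year post-CABG angiography compared to conventional SVG harvesting techniques", so it names angiography rather than CTA.

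**The concern.** The primary outcome and secondary outcomes i and ii describe the state of the same grafts but draw on different images. The sponsor recognised that a single scan at one year misses failures found earlier, and widened the source for the primary endpoint. The neighbouring outcomes were not widened.

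Outcome ii combines significant stenosis with total occlusion, so a reader will expect it to contain every graft occlusion counted in the primary. As worded it need not. A severe stenosis found early and stented may appear in no graft outcome at all.

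The loss is also unlikely to be random. Section 1 cites a trial in which patients with an occluded vein graft had thirteen times the composite of death, late infarction or repeat revascularization. Grafts that come to early imaging and rescue are therefore likely to be among the failed ones.

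**Working it through.** **1. One graft followed through the definitions.** Suppose a study vein graft is imaged for symptoms at 5 months, reopened, and shows under 50% stenosis on the 1-year CTA.

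| Finding at 5 months | Primary (graft part) | Outcome i | Outcome ii | Composite iv |
|---|---|---|---|---|
| Totally occluded | event | no event | no event | event, if the procedure meets the definition |
| 90% stenosis | no event (not an occlusion) | no event | no event | event, if the procedure meets the definition |

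The first row is the containment failure. The second is graft disease that no graft outcome records. A related case is the patient with an early clinical angiogram who misses the 1-year study: there are data for the primary but no value for i or ii.

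**2. The plan's own figures reproduce.** Inputs from section 8.5: 20% vs 14%, two-sided alpha 0.05, power 80%, 80% imaged.

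n = [1.960·√(2·0.17·0.83) + 0.842·√(0.20·0.80 + 0.14·0.86)]² / 0.06² ≈ (1.041 + 0.446)² / 0.0036 ≈ 614.1, rounded up to 615 per group.

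615 / 0.80 = 768.75, so 769 per group. Imaged patients: 0.80 × 1,550 = 1,240. None of these figures is in dispute, and the fix changes none of them.

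**3. Number of patients.** The protocol gives no rate of graft rescue, so 1-4% is an assumption. It applies to imaged patients, because a graft can be read as open only if it is scanned.

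- 1% × 1,240 = 12.4
- 4% × 1,240 = 49.6

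So about 12-50 patients. This is an upper reading: it supposes that every rescue concerned a graft, was imaged before 9 months, and left the graft under 50% stenosed at one year.

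**4. Effect on the contrast (illustration).** No stenosis rate is given, so the 20% and 14% occlusion rates stand in, with 615 grafts per group. If shares f_c and f_t of failed grafts are reopened and then read as open, the observed rates are 0.20(1 − f_c) and 0.14(1 − f_t). Power is Φ{[|p₁ − p₂|·√615 − 1.960·√(2p̄q̄)] / √(p₁q₁ + p₂q₂)}.

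| Share reopened, control / no-touch | Observed rates | Difference (points) | Relative reduction | Power |
|---|---|---|---|---|
| 0 / 0 | 20.0% / 14.0% | 6.0 | 30.0% | 80.1% |
| 5% / 5% | 19.0% / 13.3% | 5.7 | 30.0% | 77.6% |
| 10% / 10% | 18.0% / 12.6% | 5.4 | 30.0% | 74.9% |
| 20% / 20% | 16.0% / 11.2% | 4.8 | 30.0% | 69.0% |
| 10% / 5% | 18.0% / 13.3% | 4.7 | 26.1% | 62.1% |
| 5% / 10% | 19.0% / 12.6% | 6.4 | 33.7% | 86.9% |

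With a mean failure rate of 17%, shares of 5% and 20% correspond to 0.85% and 3.4% of imaged patients, close to the range assumed in step 3. Equal shares shrink the absolute difference and leave the relative reduction unchanged. Unequal shares can move both in either direction.

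**The case against.** The strongest reply is that the protocol never says clinical angiograms are excluded from the secondary outcomes. The primary is itself worded on the 1-year CT scan and then broadened, and the secondary wording could be the same shorthand, especially as the section 2 objectives say angiography. This has some force for modality. A reader might infer that patients sent to conventional angiography (under 2%, so fewer than about 25 of 1,240) have no stenosis result. That is over-literal: conventional angiography is offered to them as a substitute for the scan. The reply does not settle timing. The broadening sentence names the primary endpoint alone, and the objectives still refer to a 1-year study.

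The 9-15 month window narrows the problem. A clinical angiogram inside it can serve as the 1-year study, so the clear loss is limited to grafts imaged before 9 months. That stands.

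Reading stenosis at one scheduled time on one modality is also defensible, because it avoids symptom-driven ascertainment, and section 5.4 concedes that endoscopic patients will usually be unblinded. But the sponsor has already accepted symptom-driven imaging for the primary, and the mixed rule leaves outcome ii inconsistent with it.

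Finally, graft classification after a procedure could be left to an analysis plan or adjudication manual. The missing classification rule alone could be. The data source for i and ii is not missing, however: the protocol fixes it, and fixes it differently from the primary.

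**Conclusion.** The point holds for secondary graft outcomes i and ii in both arms, and by reference for pharmacological iii. Followed as written, outcome ii can record fewer occluded grafts than the graft part of the primary. The size is unknown and probably small: at most about 12-50 of roughly 1,240 imaged patients, under an assumed rescue rate of 1-4%.

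Three stronger readings are not supported.

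- A reader might infer that a rescued graft counts as sound throughout the secondary outcomes. It does not: the procedure can count in composite iv. Nor does the protocol state a rule that reopened grafts are sound; that result follows from the named scan and from silence on reopened grafts.
- A reader might infer a sure bias toward no difference. The absolute difference would usually shrink, but the relative reduction is unchanged under equal shares and can be inflated if more failed no-touch grafts are rescued.
- A reader might infer that the primary result or the sample size is compromised. Neither is affected. Nor should outcome ii contain the whole primary, which also includes cardiovascular or unknown-cause death; the containment argument concerns graft occlusions only.

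**What to change.** In section 5.5, Secondary Outcomes, replace the 1-year CTA in outcomes i and ii of both arms with the primary's data source: any CTA or conventional angiogram up to 15 months. Pharmacological iii then follows. Add a rule giving each graft one status:

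- **Occluded** if totally occluded on any qualifying angiogram.
- **Otherwise stenosed** if 50-99% stenosed on the 1-year study or, for a graft revascularized earlier, on the last angiogram before that procedure.
- A later, post-procedure appearance does not overwrite this status.

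The rule should also say what applies to an untreated graft with an early clinical angiogram and no 1-year study; its last qualifying angiogram is the natural choice. Outcome ii then contains every graft occlusion in the primary, and a graft stenosed early and occluded later is not counted in both i and the primary.

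The cost is a few sentences in section 5.5 and the matching adjudication instructions. The angiograms are already collected for the primary, and patient care is unchanged. The downside is that a few grafts are graded by a different modality or on symptom-driven imaging. A sensitivity analysis using only the scheduled 1-year study addresses that.
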